## Abstract

**Aims and Objectives:** To facilitate individualized assessment of unresponsive patients in the intensive care unit for signs of preserved consciousness after acute brain injury.

**Background:** Physicians and neuroscientists are increasingly recognizing a disturbing dilemma: Brain-injured patients who appear entirely unresponsive at the bedside may show signs of covert consciousness when examined by functional MRI (fMRI) or electroencephalography (EEG). According to a recent meta-analysis, roughly 15% of behaviorally unresponsive brain-injured patients can participate in mental tasks by modifying their brain activity during EEG- or fMRI-based paradigms, suggesting that they are conscious and misdiagnosed. This has major ethical and practical implications, including prognosis, treatment, resource allocation, and end-of-life decisions. However, EEG- or fMRI-based paradigms have so far typically been tested in chronic brain injury. Hence, as a novel approach, CONNECT-ME will import the full range of consciousness paradigms into neurocritical care.

**Methods:** We will assess intensive care patients with acute brain injury for preserved consciousness by serial and multimodal evaluation using active, passive and resting state fMRI and EEG paradigms, as well as state-of-the-art clinical techniques including pupillometry and sophisticated clinical rating scales such as the Coma Recovery Scale-Revised. In addition, we are establishing a biobank (blood, cerebrospinal fluid and brain tissue, where available) to facilitate future genomic and microbiomic research to search for signatures of consciousness recovery.

**Discussion:** We anticipate that this multimodal approach will add vital clinical information, including detection of preserved consciousness in patients previously thought of as unconscious, and improved (i.e., personalized) prognostication of individual patients. Our aim is two-fold: We wish to establish a cutting-edge tertiary care clinical service for unresponsive patients in the intensive care unit and lay the foundation for a fruitful multidisciplinary research environment for the study of consciousness in acute brain injury. Of note, CONNECT-ME will not only enhance our understanding of consciousness disorders in acute brain injury but it will also raise awareness for these patients who, for obvious reasons, have lacked a voice so far.

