#### Secondary objectives

We wish to pool fMRI- and EEG-based data as well as results from systematic clinical evaluations and genomic and metabolomic data to study the neuronal mechanisms by which patients regain consciousness following acute brain injury.

We will test the following hypotheses:
fMRI- and EEG-based consciousness paradigms are feasible in patients with complete (or near-complete) loss of motor function in the acute phase of brain injury.fMRI- and EEG-based consciousness paradigms, including state-of-the-art clinical rating scales and bedside techniques such as pupillometry, applied in the acute phase of brain injury, will add clinically relevant information that complements standard bedside examination. This includes detection of preserved consciousness in some patients who were clinically classified as being unconscious due to lost motor output.fMRI- and EEG-based consciousness paradigms do not always yield the same evidence for the presence or absence of consciousness in acute brain injury.Serial multimodal evaluations will better reflect a changing level of consciousness than single unimodal assessments.In most patients who regain consciousness after acute brain injury, the following pattern will be observed: Intrinsic cortical connectivity, including fronto-parietal networks, as revealed by resting state paradigms will recover first, followed by the occurrence of cognitive evoked potentials and cortical activation (passive paradigms), and lastly, the ability to follow commands (active paradigms).Because of the absence of a gold standard for consciousness (1), a composite reference standard, considering bedside examination, clinical rating scales and fMRI- and EEG-based consciousness paradigms, allows the most reliable classification of patients with DoC (16).Genomic and metabolomic data may reveal signatures for consciousness recovery.

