#### Neurological bedside examination and clinical rating scales

Patients will be assessed using a detailed neurological bedside exam performed by or supervised by board-certified neurologists with experience in neurocritical care. Patients will be examined by standardized clinical rating scales, including (but not limited to) Glasgow Coma Scale (GCS), Full Outline of UnResponsiveness (FOUR), and Coma Recovery Scale-Revised (CRS-R) (27). Examinations will be performed daily on the ward as well as directly (within 30 min) prior and after each fMRI and EEG session.

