
#### Work package 2 (clinical database, biobank)

To maximize the learning effect and to facilitate research, we will collect all relevant clinical, neurophysiological and imaging data in a comprehensive longitudinal database. This database is currently being developed, using REDCap which is provided free of charge to health care providers within the Capital Region of Denmark (45). At present, the database consists of 11 instruments (*Study ID; Cause of ICU admission; Baseline Data at ICU admission; Laboratory investigations; Neurological exam; MRI, including fMRI; EEG; Pupillometry; Neurological exam and data at ICU discharge; 3 months follow-up; and 12 months follow-up*) and at total of 555 fields (= questions). For a given patient, only a subset of these fields needs to be answered, depending on the diagnosis at admission and initial diagnostic procedures. Clinical outcome data will be assessed by a trained research nurse and a clinical PhD student, either by telephone interview or during follow up visits, using established rating scales (e.g., Coma Recovery Scale-Revised, modified Rankin Scale, Barthel index) at hospital discharge and at 3, respectively, 12 months. Target clinical data include (but are not limited to): age, sex, previous medical history (including hereditary predispositions), medication (including drugs with potential influence on consciousness levels such as antiepileptics or antidepressants), cause of admission, sedation, surgical and non-surgical complications, comprehensive laboratory investigations, neurological examination, CRS-R, GCS, FOUR, and outcome data including modified Rankin Scale (mRS), Barthel index, Glasgow Outcome Scale (GOS), as well as whether at follow-up the patient lives at home, is admitted to a rehabilitation facility, or resides in a nursing home. Neurophysiological data include (but are not limited to) resting state, passive and active EEG paradigms and (where appropriate) evoked potentials, including SSEP and BAEP. Imaging data include data from resting state, passive and active fMRI paradigms and structural MRI, including (but not limited to) T1- and T2-weighted imaging, DWI, FLAIR, gradient echo sequences and (where appropriate) MR spectroscopy and tractography. In addition, we are setting up a biobank for cerebrospinal fluid, blood and feces samples for future studies related to genomics, metabolomics and microbiomics. Minus 80° freezer facilities are available at our institution.

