### Statistical analysis

A power calculation of the required sample size that would include the combined different methods does not appear feasible owing to the multimodal design of CONNECT-ME but the numbers of patients recruited into the different work packages reflects empirical numbers derived from previous results on consciousness paradigms in the critical care setting (21, 47). In addition to descriptive statistics, we will perform correlation analysis between behavioral scales (CRS-R total score) and default mode networks, respectively, EEG entropy using Spearman testing. Non-parametric tests will be used for univariate analysis (Wilcoxon rank sum/Mann-Whitney test and Kruskal-Wallis test) to test whether default mode and other brain networks or EEG entropy differ between diagnostic groups (VS/UWS vs. MCS). Machine learning models will be applied to evaluate resting-state fMRI and other neuroimaging measures as predictors of covert consciousness and subsequent recovery (i.e., does imaging data inform patient level of consciousness and/or prognosis). Receiver operating characteristic (ROC) analysis may be used to identify a cut-off value differentiating conscious (MCS) from unconscious (coma or VS/UWS) patients. Results will be considered significant at *p* < 0.05 or lower, if appropriate (e.g., <0.001 for fMRI data). Statistical advice and supervision, including exploration with advanced machine learning algorithms, will be provided in-house (Department of Biomedical Statistics, University of Copenhagen).

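### The recovery models name only neuroimaging predictors and state no comparison with a bedside (CRS-R) model, so as written they cannot show that imaging improves prognostication beyond the bedside examination

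*Protocol article*

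**What the plan says.** **The recovery analysis.** The Statistical analysis section plans this: "Machine learning models will be applied to evaluate resting-state fMRI and other neuroimaging measures as predictors of covert consciousness and subsequent recovery". It paraphrases the question as "does imaging data inform patient level of consciousness and/or prognosis".

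**Use of the CRS-R in the same section.** The total score appears as a correlate: "correlation analysis between behavioral scales (CRS-R total score) and default mode networks, respectively, EEG entropy using Spearman testing". The same networks and EEG entropy are also to be compared between VS/UWS and MCS. The CRS-R is not named as a predictor of recovery or as a comparator.

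**The aims.** Under Secondary objectives, the paradigms, rating scales and bedside techniques such as pupillometry "will add clinically relevant information that complements standard bedside examination". The next sentence gives one component: "This includes detection of preserved consciousness in some patients who were clinically classified as being unconscious due to lost motor output". The Abstract anticipates "improved (i.e., personalized) prognostication of individual patients", and the Introduction speaks of predicting outcome better.

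**Data in hand.** On bedside scales, including the CRS-R: "Examinations will be performed daily on the ward as well as directly (within 30 min) prior and after each fMRI and EEG session". Outcome is assessed "using established rating scales (e.g., Coma Recovery Scale-Revised, modified Rankin Scale, Barthel index) at hospital discharge and at 3, respectively, 12 months".

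**The concern.** Better prognostication is a comparative claim: better than what the clinician already has, which is the bedside examination. The stated question asks only whether imaging informs prognosis. A marker that carries nothing except a noisy copy of the CRS-R would answer it yes.

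The plan itself looks for markers of this kind, since it correlates network and entropy measures with the CRS-R total and tests whether they separate the CRS-R diagnostic groups. The closer a marker tracks the CRS-R, the more readily it will predict recovery without adding anything.

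At stake is how a positive imaging-only result would be read. The Abstract and Introduction link prognosis in these patients to treatment and end-of-life decisions, so an unadjusted association taken as added prognostic value would mislead on a matter of weight.

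**Working it through.** **Is there a figure to reproduce?** No. The Statistical analysis section says a power calculation is not feasible and gives no effect size or correlation for these models. The check is therefore a comparison of claim and analysis, followed by an illustration under stated assumptions.

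**Step 1: claim against analysis.**

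| Claim | Comparison needed | Stated in the article? |
|---|---|---|
| Imaging is associated with recovery | Imaging against outcome | Yes (Statistical analysis) |
| Covert consciousness is found in patients judged unconscious | Paradigm result cross-classified against bedside diagnosis | Possible from the planned data; needs no recovery model |
| Imaging improves prognostication over the bedside examination | Bedside model against bedside plus imaging | No |

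**Step 2: illustration with zero added value.** Let x be the CRS-R at the scan, m the imaging marker and y the recovery score, all standard normal:

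- m = a·x + noise
- y = b·x + noise
- no direct link from m to y

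The unadjusted correlation of m and y is then a·b, and the partial correlation given x is 0. Inputs from the article are n = 24 (work packages 1 and 8) and the 0.05 level. Assumptions are a and b, two-sided tests, a continuous outcome, and pooling of the two packages to reach 24 + 24 = 48. Each setting used 20,000 replicates. The table gives the share with p < 0.05:

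| a = b | a·b | Spearman m–y, n = 24 | n = 48 | Partial Spearman given x |
|---|---|---|---|---|
| 0.3 | 0.09 | 7% | 9% | 5–6% |
| 0.5 | 0.25 | 20% | 37% | 5–6% |
| 0.6 | 0.36 | 37% | 67% | 5–6% |
| 0.7 | 0.49 | 64% | 92% | 5–6% |

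A hand check for a = b = 0.7 and n = 24 uses Fisher's z for a Pearson correlation: atanh(0.49) × √21 = 0.536 × 4.583 = 2.46. Power is about P(Z > 1.96 − 2.46) = P(Z > −0.50) ≈ 69%. The Spearman figure of 64% is slightly lower, as expected.

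**Step 3: the same with a binary outcome.** Recovery was made to depend on the CRS-R alone (logistic slope 1 or 2, about half recovering), with marker–CRS-R correlations of 0.3 to 0.9.

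| | Slope 1 | Slope 2 |
|---|---|---|
| AUC, CRS-R alone | 0.74 | 0.86 |
| AUC, marker alone | 0.57 to 0.71 | 0.60 to 0.82 |
| AUC, CRS-R plus marker | 0.74 | 0.86 |
| Gain from the marker | 0.000 | 0.000 |

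At n = 24 the marker alone was significant in 7% to 83% of simulated studies across these settings.

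**Step 4: how well 24 patients can measure the gain.** Penalised logistic models with 6-fold cross-validation were simulated, assuming about 50% recovery and a marker–CRS-R correlation of 0.5. A marker with no added value was added to CRS-R, age and a binary cause of injury. The change in cross-validated AUC had a central 95% range of −0.17 to +0.18, and 19% of studies showed a gain of at least 0.05. With a real effect (log-odds 1 per SD) the range was −0.10 to +0.30.

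**The case against.** **The article excludes nothing.** A reader might infer that the CRS-R has been deliberately left out of the models. The text does not say so. It lists the measures to be evaluated, and a full covariate list may sit in an analysis plan that is not shown. This stands, and the point is limited accordingly. What remains is that the question stated in the article is one of association, while the stated aims need a comparison.

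**The hypothesis is mainly about detection.** A reader might infer that the whole added-information hypothesis goes untested. It does not. Its named component, finding preserved consciousness in patients judged unconscious, already has the bedside diagnosis as comparator. Only the prognostic side is affected.

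**The clinical service does not depend on this.** A reader might infer that a misleading recovery model would trigger work package 9. That section makes the service conditional on feasibility.

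**Other analyses and outcomes exist.** Work package 5 also relates resting-state EEG to clinical outcome, so the machine learning models are not the only recovery analysis. The CRS-R is one example among several outcome scales, so the scan-time CRS-R is not necessarily the baseline of the outcome analysed.

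**The simulated rates are not false positives of the plan.** The marker really is associated with outcome, so a significant unadjusted test is correct. It becomes an error only if read as added value. The simulations also use simple tests, not the planned machine learning. Both remarks stand.

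**The remedy is imprecise at this size.** Step 4 bears this out. It is a reason for an interval and an exploratory label. It does not make an unadjusted result an answer to the comparative question.

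**Conclusion.** The point holds in a limited form. As the article words it, the recovery models can establish that imaging is associated with recovery. They cannot establish that it improves prognostication beyond the bedside examination.

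This conclusion rests on the wording: imaging predictors only are named, no bedside reference model is stated, and the question is non-comparative. It does not rest on the simulations. Those indicate how easily a pure proxy could look prognostic: from barely above the nominal level when correlations are weak (7% at 0.3) to a clear majority of studies when they are strong (64% at 0.7), for 24 patients. The real correlations are not given.

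The change is worth making because the aims are comparative and the score needed is already collected.

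**What to change.** In the Statistical analysis section:

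1. Add a bedside-only reference model for recovery using the CRS-R total from the examination before the scan. Keep it to this one covariate or very few, given 24 to 48 patients.
2. Add the imaging or EEG measures to that model. Report, with an interval, either the baseline-adjusted association (for example partial Spearman or penalised regression) or the out-of-sample change in AUC or log-loss.
3. Label this comparison exploratory, and label imaging-only models as unadjusted.
4. Claim prognostic added value only from the adjusted comparison, read with its interval.
5. Do the same for the EEG–outcome correlation in work package 5 where a bedside score is available.

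**Cost.** A few sentences and one extra model fit, with no new data. The comparison uses at least one degree of freedom, the estimate will be imprecise at n = 24, and the headline figure will probably be less favourable than an imaging-only AUC.

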### Data management, ethics approval, and patient consent

Patients enrolled into CONNECT-ME are unconscious and per definition unable to consent themselves for the study; therefore, consent will be obtained from their legally authorized representative. Patients recovering consciousness will be asked for re-consent as soon as feasible. Privacy and confidentiality is of utmost importance and data will be de-identified wherever possible. All procedures will be performed according to the Declaration of Helsinki. Approval has been obtained from the Ethics Committee of the Capital Region of Denmark (journal-nr: H-16040845) and by the Danish Data Protection Agency (RH-2016-191, I-Suite nr: 04760). As to the establishment of a biobank for future studies related to metabolomics and genomics, we will prevent genetic data from being linked to an individual's identity outside of a restricted access site. Data will be stored electronically using an independent and secure medium.

#### Registration

The study is registered with clinicaltrials.org (ClinicalTrials.gov Identifier: NCT02644265).

#### Dissemination of results and publication policy

We aim to publish results derived from this project in international peer-reviewed scientific journals as well as to disseminate relevant information to the public by local media (e.g., newspapers, TV). We will decide on authorship using consensus and Vancouver criteria at the earliest convenience on each given publication. Whenever applicable, we will allow for data sharing and provide raw data files.

### Budget, financing plan, and time schedule

All technical equipment (e.g., fMRI, EEG, pupilometer, minus 80° freezer facilities) and neurological, neurophysiological and neuroimaging expertise is in place. The home institution (Rigshospitalet, Copenhagen University Hospital) covers overhead costs. The entire time schedule covers 5 years (2 years for phase 1; 3 years for phase 2; 1 year for phase 3). Additional funding for PhD students is being applied from relevant internal, private, state and university-/hospital-based funds. At the time of writing, phase 1 is being finalized (resting state fMRI and EEG, REDCap-based clinical database; and a biobank; Figure 2). Phase 2 (clinical implementation) is scheduled for July 1, 2019—June 30, 2022).

### Lay project description

Imagine you are hospitalized and conscious but trapped in your own body—unable to move a muscle or blink with your eyes. A nightmare? Yes. But what if no one was aware of it? If your family, friends and doctors thought you didn't know what was happening around you? Research shows this is true for many thousands of patients with brain damage worldwide who are erroneously thought to be in a “vegetative state.” Fortunately, new methods can open the way to the minds of those people. With functional magnetic resonance imaging (fMRI) and electroencephalography (EEG), we can record brain responses without having to look for motor responses. Patients can be asked to think of something and the answer analyzed from their brain activity. When investigated with fMRI or EEG, 15% of patients who appear to be in a vegetative state can follow commands by performing mental tasks. These patients are conscious and misdiagnosed, which is crucial for prognosis, treatment and resource allocation. We wish to establish these methods at Denmark's largest neurocritical care unit, Rigshospitalet, Copenhagen University Hospital, and we anticipate that this will benefit patients from the entire country both in the acute stage and the chronic phase during rehabilitation.

## Discussion

Consciousness paradigms offer exciting opportunities. They improve our understanding of the biological foundations of human consciousness and, even more importantly, they allow us to assess the consciousness levels of patients with brain damage in far greater detail than previously. So far, however, they have been almost exclusively employed in rehabilitation medicine, addressing patients with chronic brain disorders, typically several years following onset of the injury. Moreover, most of these studies have been restricted to spot assessments, not considering that consciousness fluctuates over time. In addition, important methodological issues persist, including uncertainties about the specificity and sensitivity of the different paradigms and about their applicability in brain disorders of various etiologies (1). Lastly, almost all studies until now have employed either fMRI- or EEG-based paradigms, although the two modalities do not necessarily yield identical results in a given patient but rather complement each other. As we have pointed out previously, systematic evaluation of the similarities and differences of these technologies is essential, preferentially by multimodal serial assessments (1). Our group and others have recently established the feasibility of performing fMRI in the neurointensive care unit (21, 47).

The anticipated impact and learning potential of the project is significant in several ways. At the clinical level, CONNECT-ME has distinct practical implications for individual patients. Our recent meta-analysis shows that many thousands of patients worldwide are mistakenly believed to be in a “vegetative state” (1). Fortunately, there is help on the way—new imaging and neurophysiological methods allow insights into the mental world of these patients. The present project is crucially important for unresponsive patients with acute brain injury who, for obvious reasons, have lacked a voice so far. Therefore, we have named it “CONNECT-ME.”

At a more general scientific level, CONNECT-ME addresses fundamental scientific questions about the origin of human consciousness. How consciousness occurs, i.e., what it is that produces the content of our consciousness, belongs to the great existential human questions for which we lack a satisfactory answer, on the same level as the question about the origin of the universe. It is still impossible to define precisely the cerebral regions that are “minimally sufficient and collectively necessary” (48) for consciousness to occur, but by combining cutting-edge clinical, electrophysiological and neuroimaging paradigms we hope that CONNECT-ME will make a humble contribution to solve this question in the not-so-distant future.

A complex project as CONNECT-ME is subject to potential obstacles, which requires careful risk assessment. First, CONNECT-ME is deeply rooted in the clinical hospital setting—the idea is to take advantage of as many routinely collected clinical data as possible (i.e., clinical, neurophysiology, imaging, laboratory, and similar data). Unfortunately, clinicians often find it hard to act as idea generators for applied research due to an ever-increasing administrative burden and the need for more and more efficient working structures. Similarly, scientists may struggle to allocate time for a discourse with clinicians because increasingly fierce competition for limited funding requires instant scientific results. Further strain on local resources and lack of adequate funding might thus be a cause of concern.

Second, reflecting everyday clinical management of critically ill patients, CONNECT-ME will likely be subject to enrollment bias. On one hand, unstable vital functions of ICU patients may compromise their assessment by MRI (and hence their inclusion into CONNECT-ME) and create a bias to include cases with more benign prognosis. On the other hand, MRI is sometimes ordered to better visualize the extent of (usually ischemic or anoxic) brain damage to inform a decision on treatment withdrawal, thereby possibly creating a bias in the opposite direction and toward more sinister prognosis.

Third, it may turn out that only a minor subset of clinically unresponsive patients in the intensive care unit will profit from active EEG- and fMRI paradigms given the need for vigilance and the ability to follow commands required to participate in abstract mental tasks. Still, as shown in a recent paper such cognitive-motor dissociation does occur in the intensive care setting (47), and resting state (and possibly passive) paradigms also reveal essential information although they do not require active patient participation (21).

Fourth, as a truly multidisciplinary project, CONNECT-ME involves colleagues from the entire range of the clinical neurosciences: neurologists, neurosurgeons, neuroanesthesiologists, neuroradiologists, and neuroscientists. CONNECT-ME critically depends on close collaboration between all involved departments. Hence, adequate stakeholder management is essential. CONNECT-ME will only succeed if all team members share the work load and contribute data on an equal basis, and good stakeholder management is mandatory in this regard. Therefore, we have outlined a detailed management model, including a steering committee as outlined above (“Organization and stakeholders”).

Finally, research on unresponsive people with acute brain injury in the intensive care unit also requires ethical considerations, in particular if there is a potential for the detection of covert consciousness. Estimating the degree of consciousness in acutely-brain injured patients as well as their potential for recovering cognitive function is among the most difficult challenges that physicians are facing in the ICU. Indeed, prognostic uncertainty in the acutely comatose patient has been shown to lead to premature withdrawal of life-sustaining therapy (11). Consequently, novel indicators of consciousness and neurological recovery are urgently needed. EEG- and fMRI-based paradigms hold considerable promise because evidence of preserved neural networks or cognitive function may predict good patient outcome. Whereas, EEG can be performed at the bedside and does not expose patients to any substantial risk, conducting fMRI requires transportation to the MR scanner and thus, the patient has to the leave the comparatively safe surroundings of the ICU. In a recent paper on ethical considerations in fMRI research in acutely comatose patients, Weijer et al. have outlined six ethical issues that ought to be addressed by researchers and research ethics committees (49). We will address all of these here.

**“[Are] fMRI [and EEG] a therapeutic or non-therapeutic procedure in the study context?”** The first issue addressed by Weijer and co-workers is about the sufficiency of the evidence base and whether or not fMRI can be regarded as a therapeutic procedure (49). Is the belief justified that the use of fMRI in the study may benefit research participants? We will use the data derived from fMRI- and EEG-based paradigms with the greatest caution while the implementation of these paradigms is on-going (work packages 1–8). However, once they have been established as clinical routine (work package 9), fMRI- and EEG-based paradigms will certainly improve diagnosis at the single subject level. In other words, at the beginning the procedures may be considered non-therapeutic; however, over the course of the study we aim for participants to benefit individually from the fMRI and EEG paradigms, and our intention is to establish fMRI as a therapeutic procedure as the present study evolves.**“Have the risks of research participation, including the risks of intrahospital transport, been minimized consistent with sound scientific design?”** Neurophysiological assessment is associated with no particular risk and can be performed at the bedside. fMRI requires transportation of the patient into the MR scanner; however, the fMRI procedure itself is comparable to a routine clinical MRI session in terms of logistics. EEG and fMRI paradigms will be performed only when cardiorespiratory function has been stabilized, sedation has been or can be safely stopped or reduced to a level that is deemed to be consistent with obtaining useful information from the fMRI images; and no other diagnostic or therapeutic procedures are urgently pending. Patient transportation and procedures will be supervised by experienced anesthetists using state-of-the-art equipment. All procedures will be documented in the patient charts.**“Are the risks of non-therapeutic procedures no more than a minor increase above minimal risk?”** Weijler et al. state that the minimal risk threshold only applies in studies in which fMRI is a non-therapeutic procedure. Thus, this issue is relevant only to the first two phases of the present project (work packages 1–8) (49). As outlined above, we will take all necessary precautions to decrease the risk of the transportation. In addition, fMRI scans will be combined with clinically indicated structural scans where feasible.**“Have study participants been selected equitably?”** Participants must be able to tolerate lying flat in the MRI scanner. Patients with high dose sedation, seizure activity or a high risk of serious adverse events will be excluded from study participation.**“Will valid surrogate consent for study participation be obtained?”** Written accept will be obtained from the patient's legal representatives, as the patients are per definition unable to consent themselves for the study at inclusion. If the patient regains consciousness to a sufficient degree, consent will be obtained again. Withdrawal from the study is possible at any given time point without explanation. Withdrawal will not influence diagnostic or therapeutic considerations by the clinical team.**“Are adequate plans in place to share summary and individual research results with the responsible physician or the family?”** A summary of the research results will be shared with the patient or next-of-kin as well as with the treating physicians, if requested (work package 1–8). Once fMRI- and EEG-based paradigms are an established clinical service (work package 9), a detailed account of the results will be made available to patients, the family and all involved physicians on a routine basis.

How will knowledge derived from technology-assisted consciousness evaluation influence our treatment decisions? Concerns may arise primarily around false negative evaluations (i.e., suggesting erroneously that patients are in a VS/UWS, whereas in fact, they are conscious) that may lead to withdrawal of therapeutic resources. However, it should be noted that technology-assisted evaluation merely compliments the bedside evaluation which in itself is flawed. Indeed, as many as 40% of non-communicating patients with DoC are erroneously classified clinically as being in the vegetative state (5). Thus, although we agree that self-fulfilling prophecy must be avoided, the ethical dilemma introduced by technology-assisted evaluation of consciousness reflects already well-known uncertainties in daily decision making in the ICU (49). As is the case for clinically routine diagnostic and prognostic procedures, we will exert the utmost caution when incorporating the results of fMRI- and EEG-based paradigms in prognostic considerations. Indeed, results from these paradigms will only be made available to the attending clinicians after successful completion of the relevant work packages.

